## Abstract

**Background:**

Functional constipation is a common disorder worldwide and is found in all paediatric age groups. Functional constipation can be caused by delayed colonic transit or dysfunction of the pelvic floor muscles. Standard medical care in paediatric practice is often based on clinical experience and mainly consists of a behavioural approach and toilet training, along with the prescription of laxatives. Evidence to evaluate the effectiveness of pelvic physiotherapy for this complaint is lacking.

**Methods/design:**

A two-armed multicentre randomised controlled trial has been designed. We hypothesise that the combination of pelvic physiotherapy and standard medical care will be more effective than standard medical care alone for constipated children, aged 5 to 17 years. Children with functional constipation according to the Rome III will be included. Web-based baseline and follow-up measurements, scheduled at 3 and 6 months after inclusion, consist of the numeric rating scale in relation to the perceived severity of the problem, the Strength and Difficulties Questionnaire and subjective improvement post-intervention (global perceived effect). Examination of the pelvic floor muscle functions, including digital testing and biofeedback, will take place during baseline and follow-up measurements at the physiotherapist. The control group will only receive standard medical care, involving at least three contacts during five months, whereas the experimental group will receive standard medical care plus pelvic physiotherapy, with a maximum of six contacts. The physiotherapy intervention will include standard medical care, pelvic floor muscle training, attention to breathing, relaxation and awareness of body and posture. The study duration will be six months from randomisation, with a three-year recruitment period. The primary outcome is the absence of functional constipation according to the Rome III criteria.

**Discussion:**

This section discusses the relevance of publishing the study design and the development of the presented physiotherapy protocol. It also addresses difficulties when interpreting the literature with regard to the effectiveness of biofeedback, potential confounding, and future research indications. To our knowledge, this article is the first to describe the design of a randomised controlled trial among children with constipation to assess the effect of pelvic physiotherapy as an add-on to standard medical care.

**Trial registration:**

Current Controlled Trials NL30551.068.09

## Background

Constipation is a common disorder worldwide, affecting 0.7% to 29.6% (median 12%) of children aged 0–18 years, and is found in all paediatric age groups with a severity that ranges from mild to severe and a duration that ranges from brief to chronic [1-4]. Symptoms of constipation are included in the Rome III criteria (Table 1), which were formulated by paediatric gastroenterologists in 2006 [3,5]. Constipation has a major impact on a child’s psychosocial functioning. About 40% of these children are burdened by emotional problems, such as eating disorders, truancy, family problems, social isolation and depression [6-10].

**Table 1 T1:** Paediatric Rome III criteria* for childhood constipation

**Must include two or more of the following in a child with a**	
**developmental age of least four years**	
1	Two or fewer defaecations in the toilet per week
2	At least one episode of faecal incontinence per week
3	History of retentive posturing or excessive volitional stool retention
4	History of painful or hard bowel movement
5	Presence of a large faecal mass in the rectum
6	History of large diameter stools that may obstruct the toilet

*Criteria fulfilled at least once per week for at least two months prior to diagnosis, with insufficient criteria for diagnosis of irritable bowel syndrome.

The pathophysiology of childhood constipation is multifactorial and not yet fully understood. No clear organic cause is found in over 90% of the children who suffer from constipation, so-called functional constipation (FC). FC includes delayed colonic transit and dyssynergic defaecation. In the majority of children dyssynergic defaecation is the cause for their complaints, and refers to an incomplete evacuation of faeces due to paradoxical contraction of, or failure to relax the pelvic floor muscles when straining and/or a failure to increase intra rectal pressure [11,12]. In some patients, delayed colonic transit may be the result of dyssynergic defaecation. Approximately 50% of children show this abnormal defecation pattern [13]. Withdrawal of stool, hard painful defecation or fear of stool, resulting in a vicious circle, is the most commonly proposed explanation of the aetiology of dyssynergic constipation in children [4,7,12,14-16].

The standard medical care (SMC) for FC children in routine paediatric practice is often based on clinical experience and mainly consists of a behavioural approach and toilet training along with the prescription of laxatives, sometimes supported by disimpaction or a high fibre diet [7,10,14,17,18]. Despite intensive medical and behavioural treatment long-term follow-up studies have shown that 50% of the children still have complaints of constipation after five year follow up [19].

Since dyssynergic dysfunction of the pelvic floor is the major reason for FC in children, it is thought that pelvic physiotherapists, who have specific expertise in treating dyssynergic dysfunction, as musculoskeletal experts might play an important role to increase the success rate. All prerequisites for proper micturition and defecation, such as a relaxed toilet posture [18,20], adequate straining [18,21,22] and trunk stability [23-26], are trained extensively. Pelvic floor muscle training involves training the right use of the pelvic floor muscles (PFM) during contracting and straining, breathing and changes in abdominal pressure [21,22,27]. In case of (urine) incontinence, the treatment can be extended with additional PFM exercises.

Standard pelvic physiotherapy (PPT) care for the constipated child has not been described. In most cases, PPT consists of education, demystification, the use of micturition and defecation diaries, toilet training, breathing and relaxation exercises and pelvic floor muscle training (PFMT), with PFMT including exercises and biofeedback (BF) [28,29].

## Methods/design

### Trial design, hypothesis and research

To date, there has been little scientific evidence evaluating the effectiveness of pelvic physiotherapy (PPT) in childhood constipation [7,14,29,30]. Therefore we designed a two-armed multicentre randomised controlled clinical trial (RCT). We hypothesise that the combination of standard medical care (SMC) and PPT will prove more effective than SMC alone for the treatment of FC in children aged 5 to 17 years.

Secondary research questions are: (1) Does PPT add to the child’s quality of life, as defined by the strengths and difficulties questionnaire (SDQ), the numeric rating scale (NRS) in relation to the perceived severity of the problem and the global perceived effect (GPE), (2) what values of the pelvic floor muscle function (PFMF) in children can be defined based on the results of the study in clinically relevant subgroups, according to the international continence society (ICS) criteria.

### Ethical approval

This study was registered in the Netherlands National Trial Register (NL30551.068.09). The Medical Ethics Committee of the Maastricht University Medical Centre has approved the study. This study has been designed in accordance with the Helsinki Accords and the Dutch Medical Research Involving Human Subjects Act (WMO).

### Framework of the study

A child’s participation to the study starts and ends with a visit to a paediatrician. In our multicentre randomised controlled trial, the control group will receive only standard medical care (SMC) (Figure 1) whereas the experimental group will have SMC supplemented with PPT (Figure 2). The control group will have at least three contacts with the paediatrician in five months while the experimental group will have a maximum of six contacts with the physiotherapist. The study duration will be six months from randomisation, with a three-year recruitment period.

**Figure 1 F1:**
[figure not shown]
Flowchart of the randomised controlled trial.

**Figure 2 F2:**
[figure not shown]
Standard medical care in accordance with the ‘Dutch guideline on constipated children’.

### Measurement and timing

Web-based measurements will be obtained before the first visit to the physiotherapist (M-WB 1), three months after randomisation (M-WB 2) and before the final visit to the physiotherapist (M-WB-3) (Figure 1). Shortly before randomisation (M-PPT 1) and at six month, adjacent to M-WB 3, measurements at the physiotherapist will take place (M-PPT 2). After M-PPT 2 a final visit at the paediatrician is scheduled.

Web-based measurements include a structured patient reported outcome, which assesses the presence of the Rome III criteria and laxative use, co morbidity (such as urinary problems and abdominal pain), the Strength and Difficulties Questionnaire (SDQ), the numeric rating scale (with regard to experienced burden) and a two weeks diary. At follow-up (M-WB 2 and M-WB 3) the web-based measurements are supplemented with the global perceived effect (GPE).

At the last visit at the paediatrician, use of laxatives and the presence of Rome-III-criteria (primary outcome) are recorded.

### Participants

#### Study population

Children living in the Netherlands and referred to pelvic physiotherapy by paediatricians from various hospitals will be enrolled in this study.

#### Inclusion criteria

(1) age 5–17 years, (2) functional constipation according to the Rome III criteria, (3) attending regular schools, (4) parent(s) sign(s) an informed consent, (5) children aged over 11 years sign an informed consent themselves, and (6) the child and parent(s) are motivated to participate in the study.

#### Exclusion criteria

(1) prior physiotherapy because of defecation or micturition complaints, (2) urotherapy by another professional (nurse, psychologist etc.) at the start of the study, (3) severe delay in motor skills development, (4) endocrine and metabolic disorders (hypothyroidism, hypercalcemia, diabetes mellitus, diabetes insipidus), (5) neurological and psychiatric disorders (spina bifida, cerebral palsy, anorexia nervosa, autism or PDD-NOS), (6) Down Syndrome, (7) Hirschsprung disease, (8) at least 14 points on the Strength and Difficulties Questionnaire, (9) drug-induced constipation and (10) intestinal surgery (except appendectomy).

### Interventions

#### Standard medical care

Standard medical care, provided by paediatricians, will be given in accordance with the Dutch guideline for constipated children (Figure 2) [18]. Essentially, standard medical care consists of education and demystification about the complaint, food, and drink and physical activity as well as toilet training and the use of diaries and laxatives [18]. Usual care laxative use in children with faecal impaction and older than two years is 1–1.5 g /kg per day for a maximum of seven days. The maintenance dose is 0.3 to 0.8 g/kg per day [18]. The dose will be tailored to individual needs during the trial with guidance of the Bristol Stool Form Scale [31].

#### The Dutch pelvic physiotherapy protocol

In order to standardise pelvic physiotherapy (PPT) for these children, a survey was first held among 63 Dutch specialised physiotherapists. Extensive agreement existed on providing information, the use of diaries, toilet training, pelvic floor muscle training and biofeedback. On the basis of the survey a provisional PPT protocol was designed in consultation with 25 physiotherapists who were experienced in treating constipated children, using the data from the survey and the literature (Figure 3). Next, the Delphi method was used to discuss, improve and practise the interim protocol during three meetings with all participating physiotherapists. The resulting Dutch pelvic physiotherapy protocol (DPPP) (Figure 4) provides standardisation of intake and intervention.

**Figure 3 F3:**
[figure not shown]
Development of the Dutch pelvic physiotherapy protocol for functional constipation in children.

**Figure 4 F4:**
[figure not shown]
Dutch pelvic physiotherapy protocol’*.

In this study, according to the DPPP, the PPT intake will consist of medical history tracking, physical examination of at least balance and stability according to M-ABC-2, [24,32,33] assessment of breathing and straining [21,22,25,26], the Beighton hyper mobility score [34,35] and assessment of the pelvic floor muscles and their function [12,29].

The PPT intervention, with a maximum of six sessions will include standard medical care (education, demystification, toilet training, use of diaries and guiding the use of laxatives without intervention of the paediatrician and pelvic floor muscle training using exercise therapy, myofeedback (MFB) and rectal balloon training (RBT), as well as attention to breathing, relaxation and awareness of body and body posture. Awareness of urge and coordination of the PFM during filling and straining will be practised. During MFB, the child will receive information about the activity of the pelvic floor muscles by means of a visual display or a beeping sound. Children with an insensitive rectum will be taught to excrete smaller volumes and to repeat this action until a more normal level of sensory threshold is reached. In the case of an incorrect straining technique, RBT can be applied to learn to strain adequately.

The PPT will be patient-tailored and the sequence and intensity of PPT depends on the child's age and motivation, parents` motivation, co-morbidity and cognition. Toilet training, including pelvic floor muscle training, will be the basis of the PPT and requires considerable attention. All exercises, materials and methods will be presented in a playful manner and in accordance with the children’s age, loco motor skills and perceptions [24,28,29,36].

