#### Primary outcome measure

The primary outcome measure is the absence of FC according to the Rome III criteria. The use of less than 10 g of macrogol 3350 or 4000 a day, as a maintenance dose, is allowed.

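### Adjusting the group comparison for number of sessions conditions on part of the treatment and can bias the adjusted odds ratio; secondarily, the add-on wording is safe only if paediatric care is the same in both arms

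*Protocol article*

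**What the plan says.** **Adjustment.** Under Data analysis, the article plans a Pearson chi-square (or likelihood ratio) test for dichotomous outcomes, then multivariable logistic regression that takes account of any difference in the mean number of sessions. The Discussion explains that unequal numbers of protocolised contacts could produce a Hawthorne effect. The means are expected to be equal, but adjusted differences will be analysed anyway. Data analysis names age and gender as possible effect modifiers and urinary incontinence, enuresis and abdominal pain as possible confounders. The Discussion adds laxative use to the confounders, without a time point.

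**Contacts.** Framework of the study gives controls at least three paediatrician contacts in five months and experimental children at most six physiotherapist contacts.

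**Content of the arms.** The hypothesis is that "the combination of standard medical care (SMC) and PPT will prove more effective than SMC alone". Framework of the study says "the experimental group will have SMC supplemented with PPT", and the abstract's aim is "to assess the effect of pelvic physiotherapy as an add-on to standard medical care". The Standard medical care section states: "Standard medical care, provided by paediatricians, will be given in accordance with the Dutch guideline". But the abstract also says "The physiotherapy intervention will include standard medical care", and The Dutch pelvic physiotherapy protocol lists among the physiotherapist's tasks "guiding the use of laxatives without intervention of the paediatrician".

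**Endpoint.** The primary outcome is absence of functional constipation by Rome III; use of less than 10 g "of macrogol 3350 or 4000 a day, as a maintenance dose, is allowed".

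**The concern.** Randomisation already balances, in expectation, everything fixed before allocation. Number of sessions is not such a variable: it follows from the allocated treatment and from how the child fares. The article says that the intensity of physiotherapy is tailored to age, motivation, co-morbidity and cognition, all of which may also bear on prognosis. Children with the same number of sessions in the two arms need not be comparable, so the adjusted odds ratio no longer compares like with like. It could be read as the fairer, Hawthorne-free estimate when it may be the more biased one.

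The same applies to laxative use if the on-trial value is entered, because that too arises after randomisation and dose bears on the primary outcome.

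The secondary matter is attribution. If the physiotherapist takes over standard care content and laxative guidance in one arm only, a difference in success belongs to the whole package and not to physiotherapy added to otherwise identical care.

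**Working it through.** **1. The plan's own figures.** Inputs from Power of the study: 60% vs 75%, two-sided alpha 0.05, power 80%, 20% drop-out, 367 children. The pooled two-proportion formula gives 152 per arm, and 2 × 152 × 1.2 = 365. The unpooled formula gives 150 per arm, and 2 × 150 / 0.8 = 375. Both are close to 367, and the sample size is not in dispute. The planned crude odds ratio is (0.75/0.25) / (0.60/0.40) = 3 / 1.5 = 2.0.

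**2. What adjusting for sessions does.** The article gives no data on sessions, so this is an illustration with assumed inputs:
- unmeasured severity U has mean 0 and SD 1 in both arms;
- sessions = 4 + 1.5 × (experimental arm) + 0.8 U + noise with SD 0.8, rounded and limited to 1–9 (the six-contact cap is not imposed);
- log-odds of success = 0.5 − 0.8 U, plus any treatment effect;
- a laxative indicator depends on U but not on arm.

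Ignoring rounding and limits, the regression of U on sessions within an arm has slope 0.8 / (0.8² + 0.8²) = 0.8 / 1.28 = 0.625. At an equal number of sessions, the experimental child is therefore 0.625 × 1.5 = 0.94 SD less severe. That alone contributes about 0.8 × 0.94 = 0.75 to the log-odds, an odds ratio near exp(0.75) = 2.1. Averaging over the remaining variation in severity, and the laxative term, pull it somewhat lower.

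Simulated results (400,000 children), adjusting for sessions and the laxative indicator:

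| Assumed truth | Crude OR | Adjusted OR |
|---|---|---|
| No effect, 1.5 more sessions in experimental arm | 1.00 | 1.87 |
| Effect 0.8 on log-odds, 1.5 more sessions | 2.00 | 3.94 |
| Effect 0.8 on log-odds from provider or care delivery, equal sessions | 2.05 | 2.13 |
| Effect 0.8 on log-odds from physiotherapy, equal sessions | 2.03 | 2.12 |

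In the second row, adjusting for severity itself gives 2.18, so 3.94 is far off. Swapping the arm labels in the first row gives 1 / 1.87 = 0.53, so the bias can go either way. When mean sessions are equal, adjustment changes little; the small rise is what odds ratios show when a prognostic covariate is added. The adjustment is thus nearly harmless when it is not needed and can mislead when the means differ.

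**3. Add-on or package.** The last two rows cannot be told apart: within the trial, provider and arm would coincide, and no covariate separates them. Whether they do coincide is open. Framework of the study names only physiotherapist contacts for the experimental arm, and the physiotherapy protocol places laxative guidance there. Against this, the Standard medical care section does not limit paediatric care to controls.

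**The case against.** **In defence of the plan.** Unadjusted tests come first and the analysis is by intention to treat, so the session adjustment cannot affect the unadjusted comparison. Equal means are expected, in which case it would do little. Laxative use has no stated time point; the baseline value is collected and would be a proper covariate, and such detail is often left to the SAP. All of this stands. It limits the point to the adjusted estimate, but it does not justify a post-randomisation covariate as a cure for confounding.

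**Stronger readings that a reader might infer.**
- That the trial certainly compares a physiotherapist-delivered package with paediatrician-delivered care. The text does not establish this. The sentence holding the laxative phrase has an unclosed parenthesis, participation begins and ends with a paediatrician, and the flowchart and both care figures are not shown.
- That the protocol offers adjustment as a remedy for a change of provider. It does not. Sessions are tied to the Hawthorne effect, and laxatives to stool frequency and consistency.
- That laxative dosing is shown to distort the endpoint. It is not. Dose ranges follow the guideline, dose is tailored with a stool form scale, and "use of laxatives and the presence of Rome-III-criteria (primary outcome) are recorded" at the last paediatrician visit. Lower laxative need may also be a real benefit.
- That the result would turn on a few dose decisions. With about 147 per arm (367 × 0.8 / 2), 88 vs 110 successes gives p = 0.006 and 88 vs 103 gives p = 0.067. That is the general fragility of 60% vs 75% at this size, and it does not measure this defect.

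**Conclusion.** The point holds for the adjusted analysis. Allowing for number of sessions does not remove confounding from a randomised comparison and can bias the adjusted odds ratio. The 1.87 under no effect shows that the bias can be material. It rests on the assumed severity model and the 1.5-session difference, and it is not an estimate for this trial. It also rests on reading the plan as entering sessions as a covariate, which is the natural reading. The article allows no statement of size or direction. The unadjusted intention-to-treat comparison remains valid.

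The secondary point is conditional. If paediatrician-led standard care does not continue equally in both arms, the trial validly compares two care packages but cannot credit the difference to physiotherapy alone. The hypothesis's talk of a combination, and the stated aim of evaluating the Dutch physiotherapy protocol, already fit that reading; the add-on wording does not.

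**What to change.** 1. Remove number of sessions from the adjusted model. Report it by arm and by type of provider, descriptively.
2. Adjust only for variables measured before randomisation: age, gender, and baseline urinary incontinence, enuresis and abdominal pain. If laxative use is a covariate, use only the value from the first web-based measurement (M-WB 1), which precedes randomisation.
3. State whether paediatrician-led standard care, including laxative management, continues equally in both arms. If it does, correct the laxative phrase in the physiotherapy protocol and keep the add-on wording. If it does not, word the conclusion as a comparison of care packages.
4. Report by arm, beside the primary endpoint, its two parts: Rome III criteria absent, and macrogol below 10 g a day.

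**Cost:** one covariate removed, a time point fixed for another, some rewording and a short descriptive table. Rome III status and laxative use are already recorded, and the plan to use session counts implies that they will be available. The sample size does not change. The only loss is a narrower claim if the package reading applies.

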#### Primary outcome measure

The primary outcome measure is the absence of FC according to the Rome III criteria. The use of less than 10 g of macrogol 3350 or 4000 a day, as a maintenance dose, is allowed.

